## Abstract

**Graphical Abstract:**

[figure not shown]

## Background

The prognosis for patients diagnosed with hepatocellular carcinoma (HCC) is poor, with a 5-year survival rate below 20% [1]. The incidence of HCC is higher among patients who have been diagnosed with chronic viral hepatitis C and/or cirrhosis [2]. The annual incidence of HCC for cirrhotic patients due to chronic hepatitis B or C infection is 2–5% [3].

According to the guidelines of the American Association for the Study of Liver Diseases−AASLD and of the European Association for Study of the Liver−EASL, biannual ultrasonography (US) is recommended for high-risk patients [4, 5]. Advantages of US as a surveillance tool include the relatively low costs, widespread availability, and no radiation exposure. However, for patients with concurrent steatohepatitis or obesity, the accuracy of US surveillance is limited, due to impaired transabdominal US access of the liver [6, 7]. In addition, a recent meta-analysis showed that the sensitivity for detecting early-stage HCC using US is merely 47% [8]. Studies and guidelines have emphasized the importance of timely detection of early-stage HCC lesions, *i.e.*, smaller than 2 cm, as this will improve survival [9–11]. Unfortunately, HCC lesions detected during US surveillance are often larger than 2 cm [8], directly emphasizing the urgent need for better surveillance methods.

The American College of Radiology states that multiphase contrast-enhanced tomography (CT) and magnetic resonance imaging (MRI) need to be considered for HCC surveillance when US is insufficient [12]. The disadvantages of both CT and MRI include high costs, long duration, and limited availability and capacity compared to US. Furthermore, the potential risks associated with the use of intravenous contrast agents, and, regarding CT, the potential risks of repeated radiation exposure should be taken into consideration.

Studies have shown that non-contrast MRI (ncMRI) has similar sensitivity for detecting focal liver lesions as compared to gadoxetic-acid enhanced MRI [13, 14]. By using ncMRI, not only the potential risks related to contrast agents are eliminated, but the costs and duration of the examination are reduced as well. These advantages may favor ncMRI as a surveillance tool.

Hence, we have taken the first step to investigate the feasibility of a ncMRI protocol for the screening of HCC in a simulated study, evaluating this “short MRI surveillance” (SMS) protocol in 240 patients [15]. Patients underwent yearly a full liver MRI protocol (Fig. 1), of which the three sequences constituting the SMS protocol were extracted and analyzed (Fig. 1c–e). Promising sensitivity and specificity were found of 80–97% and 72–91%, respectively. We concluded that the proposed SMS protocol is highly accurate for detecting HCC in high-risk patients.

**Fig. 1 Fig1:**
[figure not shown]
Images of a patient with chronic hepatitis C cirrhosis using the full MRI liver protocol. Newly found hypervascular lesion (arrows) measuring 13 mm in diameter can be seen (**a**), showing wash-out (**b**) and hyperintensity on T2-weighted image (**c**), as well as hyperintensity on diffusion-weighted image (**d**) and hypointensity on T1-weighted image (**e**). The lesion was classified as LI-RADS 5

For the next step, we will setup a prospective, multicenter study to evaluate the SMS protocol in current surveillance patients and compare it to US.

## Methods

### Study design

The study protocol was reviewed and approved by the Medical Ethics Review Committee (MEC-2022-0731). Written informed consent will be signed and obtained from all participating patients by the investigators. This trial is registered at the international trial registry of ClinicalTrials.gov (NCT05429190).

This is a prospective, multicenter, observational patient cohort study. Patients will be recruited from the already existing US surveillance cohorts of six hospitals in the Netherlands. Patients will be invited for paired US-SMS surveillance, every 6 months (Fig. 2).

**Fig. 2 Fig2:**
[figure not shown]
Flowchart of the study design. *HCC*, Hepatocellular carcinoma; *LR-1/5*,*M*, LI-RADS-1/5,M; *MRI*, Magnetic resonance imaging; *SMS*, Short MRI surveillance; *US*, Ultrasound

### Patient recruitment and selection

The inclusion of patients will be done at (1) the Erasmus Medical Center Rotterdam; (2) the Amsterdam University Medical Center; (3) the St. Franciscus Gasthuis & Vlietland, Rotterdam; (4) the Maasstad hospital, Rotterdam; (5) the Albert Schweitzer hospital, Dordrecht; and (6) the Medisch Spectrum Twente, Enschede. The inclusion and exclusion criteria are based on the recommendations from the guidelines database from the Royal Dutch Medical Association [16] (Table 1).

**Table 1 Tab1:** Inclusion and exclusion criteria

Inclusion criteria	Exclusion criteria
- Patients age ≥ 18 years at time of enrollment - Patients diagnosed with chronic hepatitis B ◦ All patients diagnosed with chronic hepatitis B and liver cirrhosis ◦ The following patients diagnosed with chronic hepatitis B without liver cirrhosis: ▪ East-Asian men ≥ 40 years of age ▪ East-Asian women ≥ 50 years of age ▪ Patients from sub-Saharan Africa ≥ 20 years of age ▪ Patients with HCC family history - Patients diagnosed with non-hepatitis B cirrhosis: ◦ Patients diagnosed with hepatitis C ◦ Patients diagnosed with alcoholic cirrhosis ◦ Patients diagnosed with hemochromatosis ◦ Patients diagnosed with primary biliary cirrhosis	- Patients age < 18 years at time of enrollment - Patients who decline to sign the written informed consent form - Patients with contraindications for undergoing magnetic resonance imaging examination

### Sample size calculation

The sample size was determined using a procedure of 1000 simulations. Based on own preliminary results and previously reported prevalence, the prevalence of HCC in our screening population was set at 12% [17–19]. Secondly, the sensitivity and specificity of the SMS protocol was assumed be 80% and 72%, respectively, based on our own data analysis [15]. For US, the sensitivity and specificity were assumed to be 53% and 91%, respectively [8, 15]. Then, the number of true and false positives and true and false negatives were generated. Using exact binomial testing, the *p*-value from comparing US and SMS was obtained. Next, this procedure was repeated by generating 1000 datasets and investigating the proportion of samples with *p*-value below 0.05 (α-level). Finally, the sample size was determined by setting the power (1-β) at 80%. This resulted in a calculated sample size of 470 assuming a drop-out rate of 10–15%.

Furthermore, given the dynamic enrollment of the participants, we estimated that the average number of screenings will be 2.5 per patients. Using the calculated sample size, the total number of screenings over the study period will be 1,175 screenings of paired US-SMS. In addition, similar prospective studies have been carried out with comparable numbers [18, 19]. Therefore, our study cohort will have a sufficient sample size to evaluate the value of the SMS and relate to other similar studies.

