### Surveillance program

Patients enrolled into the study receive paired US-SMS surveillance with a 6-month interval, with an inclusion period of 3 years. The US surveillance will be performed by radiologists or hepatologists with at least 3 years of experience with US of the liver and upper abdomen on current clinical applied ultrasound systems. Participating centers have different brands of US systems with a model build 0.5 to 6 years ago. Reading of the US will be done by one reader who will also evaluate the SMS as one of three readers.

MRI will be performed on clinical applied 1.5-T system from different vendors using a dedicated body coil with an 8–16 channel range. The SMS will consist of three sequence parameters as specified in Table 2. Each SMS will be evaluated by three experienced and well-trained radiologists who will be blinded for each other’s findings and of which two readers will also be blinded for US findings.

**Table 2 Tab2:** Scan parameters of the short MRI surveillance (SMS) protocol on 1.5-T systems

Sequence	Matrix size	Slice thickness (mm)	Gap (mm)	Repetition time (ms)	Echo time (ms)	Flip angle (°)	Duration (min:s)
Axial, T1-weighted 3D gradient-echo in-out phase	300 × 260	4	0	6.2	2.1/4.2	12	0:16
Axial, T2-weighted fast spin-echo with fat saturation	320 × 320	6	0.5	Dependent on triggering	93.8	160	3:42 (dependent on respiratory frequency)
Axial, echo-planar diffusion-weighted (*b* = 50, 100, and 800 s/mm^2^)	120 × 150	6	0.6	Dependent on triggering	60.1	90	2:34 (dependent of respiratory frequency)

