### Endpoints

The primary endpoint of this study is the sensitivity, specificity, the positive predictive value, and an estimated negative predictive value for early-stage HCC detection by SMS with respect to US surveillance during a 3-year follow-up.

A secondary endpoint is the cost-effectiveness of SMS compared to US surveillance. It is hypothesized that despite the direct higher costs of MRI, SMS will be cost-effective. We expect that SMS will detect at least twice more early-stage HCC than US, based on calculated sensitivity and specificity of the pilot study [15]. This may allow for relative less expensive treatment with favorable patient outcome when compared with specialized liver surgery and chemotherapy regimes in case of more advanced stage HCC [21]. These differences in management and inherent costs will be addressed within the calculations of the cost-effectiveness study.

Another secondary endpoint of this study is the patient acceptance of the SMS as the potential new screening standard modality. Patients will be invited to circumvent their experiences, through a questionnaire which also allows to express their compliance with both modalities.

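### The 12% HCC prevalence behind the 80% power has no unit or time frame, and the protocol's own incidence and screening count do not support the roughly 56 cases it implies

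*Protocol article*

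**What the plan says.** Under Sample size calculation, the protocol article states that "the prevalence of HCC in our screening population was set at 12" percent, citing the group's own preliminary results and earlier reports. SMS sensitivity is taken as 80% and ultrasound sensitivity as 53%. The two are compared by an exact binomial test at 0.05 in 1000 simulated datasets. The outcome is "This resulted in a calculated sample size of 470 assuming a drop-out rate of 10–15" percent. The same section adds "we estimated that the average number of screenings will be 2.5 per patients", so that "the total number of screenings over the study period will be 1,175 screenings of paired US-SMS", and concludes that the cohort is large enough.

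Three other sections bear on the number of cancers:

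- Background: "The annual incidence of HCC for cirrhotic patients due to chronic hepatitis B or C infection is 2–5" percent.
- Study design: "Patients will be recruited from the already existing US surveillance cohorts of six hospitals in the Netherlands".
- Surveillance program: "paired US-SMS surveillance with a 6-month interval, with an inclusion period of 3 years".

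The Endpoints section words the primary endpoint "for early-stage HCC detection by SMS with respect to US surveillance during a 3-year follow-up".

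**The concern.** Only patients with HCC contribute to the sensitivity comparison, so its power depends on the number of HCC patients and not on 470 as such. The 12% sets that number, yet it has no unit and no time frame. In a cohort already screened by ultrasound, much of the yield should be new cancers arising during the study, plus whatever earlier ultrasound missed. The protocol gives a rate and an average number of screenings, and their product is well below 12%. If the yield is nearer that product, a non-significant sensitivity comparison would be read against a claimed 80% power that the study did not have.

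**Working it through.** **Inputs from the protocol.** Prevalence 12%; N = 470; drop-out 10–15%, leaving 400–423 evaluable; sensitivities 0.80 and 0.53; alpha 0.05; 2.5 screenings per patient at 6-month intervals; incidence 2–5% per year.

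**Assumptions of this check.** The test is a two-sided exact McNemar test (binomial on discordant pairs). The number of HCC patients is Binomial(N, yield). The between-test correlation among HCC patients is not stated, so three cases are used:

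- Independent misses: discordant probabilities 0.80 × 0.47 = 0.376 and 0.20 × 0.53 = 0.106.
- Correlation 0.3: 0.316 and 0.046.
- Maximum correlation (ultrasound finds nothing that SMS misses): 0.27 and 0.

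**Step 1: the stated design.** 470 × 0.12 = 56.4 expected HCC patients. Exact power under independence with all 470 evaluable is 80.7%. The 470 therefore reproduces.

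**Step 2: the yield implied by the other figures.** Counting one 6-month interval for every screening, including the first, gives 2.5 × 0.5 = 1.25 years. Counting only from first to last visit would give 1.5 × 0.5 = 0.75 years, so 1.25 is the more favourable choice.

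- 1.25 × 2% = 2.5%, and 470 × 0.025 ≈ 12 cases.
- 1.25 × 5% = 6.25%, and 470 × 0.0625 ≈ 29 cases.

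**Step 3: what 12% would require.**

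- Over 1.25 years: 12% / 1.25 = 9.6% per year.
- Over 3 years: 1 − 0.98³ = 5.9% to 1 − 0.95³ = 14.3%. A rate of about 4.2% per year gives 12%. Three years at 6-month intervals is about six screenings, not 2.5.
- Read per screening: 0.12 × 1,175 = 141 cancers.

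**Step 4: allowance for missed cancers.** Suppose the first SMS also finds cancers missed by earlier ultrasound, taken as one half-year's incidence × 0.47/0.53. This is an assumption.

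- At 2%: 0.025 + 0.010 × 0.887 = 3.4%.
- At 5%: 0.0625 + 0.025 × 0.887 = 8.5%.
- In 470 patients that is about 16–40 cases.

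**Step 5: power at N = 400 / 423 / 470.**

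| Yield | Independent | Correlation 0.3 |
|---|---|---|
| 2.5% | 8 / 9 / 11% | 7 / 8 / 11% |
| 6.25% | 39 / 42 / 48% | 51 / 55 / 62% |
| 3.4% (with missed pool) | 15 / 17 / 21% | 16 / 19 / 24% |
| 8.5% (with missed pool) | 55 / 58 / 64% | 70 / 74 / 79% |

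At maximum correlation, a 6.25% yield gives 67 / 72 / 80%. Under that assumption, 12% with 470 patients would give over 99%, which is not the design that was sized.

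**The case against.** Prevalence is not incidence. The 12% is attributed to preliminary data and cited studies that cannot be seen here. The 2–5% is a background figure for hepatitis B or C cirrhosis and not a design input. The cohort also admits other cirrhosis and non-cirrhotic hepatitis B, for which no rate is given. The missed-cancer allowance is not a ceiling: the Background says ultrasound is hampered by obesity and steatohepatitis, so misses may recur in the same patients and the pool at the first SMS could be larger. The power figures also depend on a correlation that the protocol does not state. All of this stands. It is why the point is an unreconciled input with a range of consequences, and not proof that 12% is wrong or that 80% cannot be reached.

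Three stronger readings are tempting and are not supported:

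- **That 470 is miscalculated.** It reproduces from the stated inputs.
- **That power falls short even at 12% once drop-out is taken off.** Exact power under independence is then 73–76%, but with a mid-p test it is 79–81%, and with the exact test at correlation 0.3 it is 88–90%. The protocol fixes no correlation, so no error follows.
- **That the 3-year follow-up is itself an error beside 2.5 screenings.** The protocol attributes the average to dynamic enrolment, and the three years can be read as the study window. If entry is uniform over three years (an assumption), mean time on study is about 1.5 years, or about three screenings before drop-out. Three years matters here only because it is the time frame over which 12% would fit the stated incidence.

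**Conclusion.** The point holds as an unsupported input to the sample size. The protocol plans on about 56 HCC patients, while its own screening count and only stated incidence give 12–29 in 470, about half at best. Power for the sensitivity comparison is then about 8–48% with independent misses and about 7–62% at correlation 0.3. With the assumed missed-cancer pool the ranges are about 15–64% and 16% to just under 80%. These figures rest on 1.25 years per patient, on 2–5% per year applying to the whole cohort, on a two-sided exact McNemar test and on 400–470 evaluable patients. A larger missed pool, or near-maximal correlation at the top of the incidence range, could bring power to 80% or more, but the protocol states neither. Confidence is high that the reconciliation is missing and lower for any single power figure. As the primary endpoint is worded for early-stage HCC, the informative cases may be fewer still. The statement that the cohort is large enough should not stand as written.

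**What to change.** In Sample size calculation:

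1. State whether 12% is per patient, per screening or cumulative, and over what period.
2. Justify it, or replace it, by the cumulative yield expected over 2.5 six-monthly screenings: incidence plus an explicit allowance for prevalent cancers missed by earlier ultrasound.
3. Re-run the existing simulation with a stated between-test correlation and after 10–15% drop-out.
4. Report the expected number of HCC patients and the power that follows.
5. Make the claim of adequate size conditional on reaching the required number of HCC patients: about 56 under independence, fewer with positive correlation (about 40 at 0.3).

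The cost is one re-run and a reworded section. This correction requires no extra enrolment; the downside is that the stated power is likely to be less favourable. It makes any shortfall visible but does not remove it. Under independence at a 6.25% yield, 80% power would take about 55 / 0.0625 = 880 evaluable patients.

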### Surveillance program

Patients enrolled into the study receive paired US-SMS surveillance with a 6-month interval, with an inclusion period of 3 years. The US surveillance will be performed by radiologists or hepatologists with at least 3 years of experience with US of the liver and upper abdomen on current clinical applied ultrasound systems. Participating centers have different brands of US systems with a model build 0.5 to 6 years ago. Reading of the US will be done by one reader who will also evaluate the SMS as one of three readers.

MRI will be performed on clinical applied 1.5-T system from different vendors using a dedicated body coil with an 8–16 channel range. The SMS will consist of three sequence parameters as specified in Table 2. Each SMS will be evaluated by three experienced and well-trained radiologists who will be blinded for each other’s findings and of which two readers will also be blinded for US findings.

**Table 2 Tab2:** Scan parameters of the short MRI surveillance (SMS) protocol on 1.5-T systems

Sequence	Matrix size	Slice thickness (mm)	Gap (mm)	Repetition time (ms)	Echo time (ms)	Flip angle (°)	Duration (min:s)
Axial, T1-weighted 3D gradient-echo in-out phase	300 × 260	4	0	6.2	2.1/4.2	12	0:16
Axial, T2-weighted fast spin-echo with fat saturation	320 × 320	6	0.5	Dependent on triggering	93.8	160	3:42 (dependent on respiratory frequency)
Axial, echo-planar diffusion-weighted (*b* = 50, 100, and 800 s/mm^2^)	120 × 150	6	0.6	Dependent on triggering	60.1	90	2:34 (dependent of respiratory frequency)

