### Imaging criteria for suspicious HCC lesions and confirmation

On US surveillance, a suspicious nodule is defined as follows:A nodule larger than 1 cm, previously not seen or increased in size compared to previous US;A nodule without typical features of simple cysts or hemangiomas;Impression of diffuse infiltrative lesion(s) with or without portal vein obstruction;Occurrence of thrombosis in previously patent portal or hepatic vein.

Reporting will be done according to LI-RADS US algorithm for visualization score and detection category of lesions.

With the SMS, a suspicious nodule is defined as a newly appearing or enlarging nodule that shows at least one of the following imaging features:Hypointensity on T1-weighted imaging;Hyperintensity on T2-weighted imaging;Restricted diffusivity;Nodule-in-nodule pattern (mosaic appearance);Nodule with heterogeneous fatty changes;Nodule containing blood products.

Diffuse infiltrative lesions with or without a suspected (tumor) thrombus or a new thrombus in the portal- or hepatic vein without distinct lesions will be also considered suspicious. Reporting of the SMS will be done first by quality assessment of SMS acquisition and secondly by detection category of lesions. Observations will be related to previous SMS, if available. Consensus will be reached on interpretation and registration of findings on SMS by majority vote.

In case of suspicious findings on the US or SMS, a full liver MRI protocol examination will be scheduled within 2 weeks, adopting the protocol as described by Willemssen et al. [15]. The protocol will consist of the SMS sequences and, additionally, a coronal and axial T2-weighted single-shot fast-spin echo; an axial, dynamic phase, 3D gradient echo T1-weighted image with fat suppression; contrast-enhanced axial dynamic phase, 3D gradient echo T1-weighted images with fat suppression; and a coronal, gradient echo T1-weighted image with auto calibrating reconstruction for cartesian sampling. Contrast-enhancement will be done using 7.5 cc gadobutrol 1 mmol/mL at a rate of 2 mL/sec and a saline flush of 30 mL.

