### Data storage and management

For data storage and management, we use the national imaging platform provided by CTMM/Lygature TraIT (http://www.ctmm-trait.nl/trait-tools/xnat). This platform is built on top the open source XNAT software (www.xnat.org). Users need proper authorization in order to access images and derived data, this to secure patients data. The Clinical Trial Processor software is used to transfer data from the local PACS software to the central imaging platform. Readers of the SMS will enter their findings separately into a standardized and anonymized clinical report form in the online clinical software program Castor EDC.

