### Statistical analysis

The sensitivity, specificity, positive predictive value, and an estimated negative predictive value of the SMS and US for the detection of HCC will be calculated and compared, using the results of the full MRI liver protocol as reference standard, combined with negative follow-up for the cases of no suspicious findings at US and SMS. Only an estimated negative predictive value can be calculated, due to non-availability of the full liver MRI in case of no findings on both the US and SMS. McNemar test will be used to determine significance in differences between the sensitivity and specificity of SMS *versus* US.

The cost-effectiveness analysis will be conducted from a healthcare perspective, using costs per detected cancer as outcome. Direct medical costs will be measured for both diagnostic pathways, using collected data from participating medical center databases and literature. The analysis will be carried out according to Dutch guidelines and by using a Markov model. The final outcome will be an incremental cost-effectiveness ratio to express the difference in costs between the SMS and US pathway per unit of health gain, *i.e.*, the number of detected cancer and quality adjusted life years. The uncertainty around the estimates will be addressed using deterministic and probabilistic sensitivity analyses.

In addition, data from this study and literature will be used to calculate the impact of improved detection of early-stage HCC on outcomes, *i.e.*, progression free survival and overall survival.

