## Discussion

The aim of this study protocol is to evaluate the value of the SMS and compare it to the current standard of biannual US surveillance for HCC. This is a prospective multicenter study with a paired design for a single arm of patients.

Previous studies have proven the value of HCC imaging surveillance with US when compared to no screening [22, 23]. Jespen et al. [24] suggested that it may be necessary to perform more randomized controlled trials on HCC surveillance to determine whether the benefits of surveillance weigh up against the harms and the costs. A large scale randomized controlled trial showed that semiannual screening with US reduced HCC-related mortality by 37% for those who underwent surveillance, despite suboptimal adherence to the surveillance program (58.2%) [23]. Other studies have reinforced the benefits of surveillance in high-risk patients with detection of more early-stage HCC with consequently a higher rate of curative treatments and better survival than in the non-surveillance group [25, 26]. Kim et al. [27] and An et al. [28] have published study protocols based on abbreviated ncMRI protocols. Either the patients were offered an annual screening using ncMRI or were assigned to biannual US surveillance with a cross-over study design of biannual ncMRI surveillance or US [27, 28]. We believe that our study design of paired US-SMS will allow for a direct head-to-head comparison in diagnostics and patient acceptance.

To the best of our knowledge, this is the first published paired US-MRI study design. We expect that the proposed SMS will detect at least twice as many early-stage HCC lesions and be the next step in improving the hepatitis-cirrhosis HCC care chain. Based on our preliminary results and emerging insights from the literature, we expect the projected cost-effectiveness analysis to favor SMS [13–15]. We also expect the SMS to improve sensitivity for detection of early-stage HCC as an objective surveillance imaging tool, compared to US and may gain patient acceptance as a new standard for imaging surveillance of HCC.

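### The US reader, unblinded to US, votes in the SMS majority that is tested against that same US read, so SMS is not independent of its comparator

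*Protocol article*

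**What the plan says.** Four places in the protocol article fix the arrangement.

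- Surveillance program, on who reads: "Reading of the US will be done by one reader who will also evaluate the SMS as one of three readers".
- Same section, on blinding of the three SMS readers. They do not know each other's findings, but only some are masked to US: "of which two readers will also be blinded for US findings". The one left over is the person who read the US.
- Imaging criteria for suspicious HCC lesions and confirmation, on how the three reads become one result: "Consensus will be reached on interpretation and registration of findings on SMS by majority vote".
- Statistical analysis, on the comparison: "McNemar test will be used to determine significance in differences between the sensitivity and specificity of SMS" versus US.

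The Discussion presents the intended inference: "our study design of paired US-SMS will allow for a direct head-to-head comparison in diagnostics and patient acceptance". Data storage and management adds a fact that matters for the remedy: "Readers of the SMS will enter their findings separately into a standardized and anonymized clinical report form".

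**The concern.** In a paired accuracy study, each test should be read without knowledge of the other. Here one of three SMS votes comes from someone who has read the US. Two US-blinded votes that agree settle the result. When they split, the US reader decides, and information from the comparator can enter the index test.

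There is a second, separate asymmetry. SMS is a consensus of three readers and US is one reader's result. Part of any difference may then reflect the number of readers rather than the modality.

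Sensitivity and specificity of SMS against US form the primary endpoint, and the cost-effectiveness model uses detected cancers. Both inherit whatever the reading rule adds or removes.

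**Working it through.** **Inputs from the article (Sample size calculation).** HCC prevalence 12%; SMS sensitivity 80% and specificity 72%; US 53% and 91%; N = 470; power 80%; α 0.05 (taken as two-sided).

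**Assumptions.** The article gives 80%/72% for the SMS protocol and does not say that they are single-reader values; I treat them so. Readers err independently of each other and of US unless stated otherwise.

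**1. The plan's own figure.** I used an exact McNemar test on HCC cases, with the number of cases Binomial(470, 0.12) and independent errors. The discordant probabilities are 0.80 × 0.47 = 0.376 (SMS+/US−) and 0.20 × 0.53 = 0.106 (US+/SMS−). Power is 80.6%, which reproduces 470 if 470 is the number analysed. The planned comparison is therefore 80% against 53%, a difference of 27 points.

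**2. How often the unblinded vote decides.** Two blinded readers disagree with probability 2p(1−p):
- HCC cases: 2 × 0.80 × 0.20 = 32%.
- Non-HCC cases: 2 × 0.28 × 0.72 = 40%.
- At a latent correlation of 0.8 between readers (simulation): 14% and 17%.

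**3. What the third vote does.** With p the chance that a blinded reader calls positive and p3 that of the third reader, the majority is positive with probability p² + p3 × 2p(1−p).

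If the third reader calls positive when either the SMS or the US looks positive:
- HCC: p3 = 1 − 0.20 × 0.47 = 0.906; majority = 0.64 + 0.906 × 0.32 = 0.930.
- Non-HCC: p3 = 1 − 0.72 × 0.91 = 0.345; majority = 0.0784 + 0.345 × 0.4032 = 0.217, so specificity is 78.3%.

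| SMS result | Sensitivity | Specificity |
|---|---|---|
| One blinded reader | 80.0% | 72.0% |
| Majority, all three blinded | 89.6% | 80.9% |
| Majority, third also calls every US-positive | 93.0% | 78.3% |
| Majority, third simply repeats US | 81.0% | 88.5% |

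Against three blinded readers, carry-over adds 3.4 points of sensitivity and costs 2.6 points of specificity. At latent correlations of 0.3 to 0.8 these become about 2–4 and 1–2 points.

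**4. The McNemar cells among HCC cases.** With three blinded readers, US+/SMS− is 0.53 × (1 − 0.896) = 5.5%. With carry-over, a US-positive case is SMS-negative only if both blinded readers miss it: 0.53 × 0.20 × 0.20 = 2.1%. SMS+/US− stays at 0.47 × 0.896 = 42.1%. Carry-over thus removes only pairs that count for US. The change of 3.4% is about 2 of the roughly 56 expected HCC cases (12% of 470).

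**5. Equal true sensitivity.** Take 53% for a single SMS read and for US, with 411 analysed (470 less 12.5%, the middle of the stated drop-out range). The exact McNemar test rejects 3% of the time for one blinded SMS reader against US, 3% for three blinded readers, and 28% under full carry-over, where SMS sensitivity becomes 66.9%.

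**6. Reader number alone.** Majority of three blinded readers against one: 89.6 − 80.0 = 9.6 points of sensitivity and 80.9 − 72.0 = 8.9 points of specificity if independent; about 1 point each at a latent correlation of 0.8.

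**The case against.** A reader might infer that the arrangement biases the whole comparison toward SMS, by as much as 93.0 − 80.0 = 13 points of sensitivity. The documents do not support that. Of the 13 points, 9.6 come from majority voting under fully independent errors, the extreme case for three people viewing the same images. Only 3.4 come from unblinding. Specificity is also part of the primary endpoint, and against three blinded readers carry-over lowers it. A third reader who repeats the US result gives about 78–81% sensitivity across the correlations tried, which is below three blinded readers. Nor is the reading order stated: a US reader who had already seen the SMS could carry information the other way.

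A reader might also suppose that the unblinded vote falls on exactly the cases McNemar counts. Those are different sets: the vote decides when the two blinded SMS readers disagree with each other, whereas McNemar counts disagreement between SMS and US.

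There is a real safeguard. Two blinded readers who agree always outvote the third, so no SMS is positive without at least one US-blinded positive vote. A declared three-reader consensus is also a legitimate index test, although it describes a three-reader programme.

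These points limit the direction and size. They do not restore independence: the article itself counts the unblinded vote in the SMS result, and this is not a detail left to another document.

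**Conclusion.** The point holds as a loss of independence in the primary comparison. By the article's own reading rule, the SMS result depends in part on the US read it is tested against, and a three-reader consensus is compared with a single read.

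If the US reader carries US-positives over, SMS gains about 3 points of sensitivity and loses about 2.6 points of specificity relative to three blinded readers. That rests on single-reader values of 80%/72%, independent errors and complete carry-over. The direction for sensitivity depends on reader behaviour, so a uniform bias toward SMS is not shown. The reader-number effect is distinct, from about 1 to 9.6 points of sensitivity depending on how strongly readers' errors correlate. Without reader agreement and reading order, neither size can be fixed from the article.

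**What to change.** Make the primary SMS result US-blinded. Take the separately entered reads of the two US-blinded readers, compare each with US, and combine them by a pre-specified paired method that allows for two reads per examination, for example GEE clustered by patient. An ordinary McNemar test does not fit reader-averaged results, and a vote of two has no tie rule, so the method must be named in advance. This also gives a single-reader against single-reader comparison. Report the three-reader majority vote as secondary.

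Where reader allocation already permits, the US reader can instead be left out of that patient's SMS panel. The article does not show whether this is feasible across the six centres. State the reading order as well, because blinding the SMS readers does not protect the US read from knowledge of SMS.

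Leave the trigger for the full liver MRI work-up as it is; only the analysis changes.

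Cost: analysis wording, with no new readers or reads for the main fix. The SMS estimate may be somewhat less favourable. A blinded reader's outvoted positive with a negative US is verified only by follow-up, and the report should say so.
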